## Abstract

**Background:**

Physical activity can improve many common side effects of cancer treatment as well as improve physical function and quality of life (QOL). In addition, physical activity can improve survival rate and reduce cancer recurrence. Despite these benefits, only 23% of cancer survivors in England are active to recommended levels. Cancer survivors are interested in lifestyle behavior change. Home-based interventions offer a promising means for changing physical activity behavior. Prediagnosis levels of physical activity and self-efficacy have been reported to be predictors of physical activity behavior change. The Move More Pack, which has undergone revision, is a printed resource with supporting Internet-based tools that aims to increase the physical activity of cancer survivors in the United Kingdom. The revised Move More Pack is underpinned by the theory of planned behavior and the social cognitive theory.

**Objective:**

The aim of this proposed study was to investigate the effect of the revised Move More Pack, supported by Internet-based tools, on physical activity, self-efficacy, and health-related QOL (HRQOL) of cancer survivors in the United Kingdom.

**Methods:**

This study is a two-arm waiting list randomized control trial with embedded process evaluation. A sample of 99 participants per arm will be recruited by invitation through an email database of cancer survivors held by UK charity Macmillan Cancer Support and an advert placed on the Macmillan Cancer Support Facebook page. Each participant is randomized to receive brief physical activity information and the UK guidelines for physical activity, or brief physical activity information and the revised Move More Pack with supporting Internet-based tools. The intervention and control arm will be followed up at 12 weeks to identify changes in self-reported physical activity, self-efficacy, and HRQOL based on Web-based questionnaires. The control arm will receive the revised Move More Pack at 12 weeks with follow-up at 24 weeks. The intervention arm is followed up at 24 weeks to determine maintenance of reported changes. Subgroup analyses will be completed based on participants’ prediagnosis level of physical activity and baseline self-efficacy as possible predictors of positive changes. Use of each component of the revised Move More Pack will be assessed using a 4-point Likert scale. Semistructured phone interviews will evaluate the use and perceived usefulness of the revised Move More Pack.

**Results:**

Participant recruitment started in March 2017. Projected completion of this study is October 2018.

**Conclusions:**

This study’s findings will identify if the proposed low-cost broad reach intervention improves physical activity, self-efficacy, and the HRQOL of cancer survivors. The process evaluation is designed to contextualize the use and perceived usefulness of the revised Move More Pack, help augment its efficient distribution, and identify potential improvements to its design.

## Introduction

### Physical Activity in Cancer Survivors

Two and a half million people are living with or beyond cancer in the United Kingdom [1]. In the last 5 years, this number has grown by almost half a million [1]. The number of cancer survivors, that is, someone living with or after any form of cancer diagnosis [2], is expected to rise to 4 million by 2030 [1].

Developing cancer depends on factors such as age, genetics, and lifestyle behaviors, with a suggested 40% of all cancer diagnosed in the United Kingdom linked to tobacco, alcohol, unhealthy diet, being overweight, and inactivity [3]. Leading a physically active lifestyle reduces people's risk of developing several cancers [4].

Being physically active has multiple benefits for cancer survivors. Physical activity can improve many common side effects of cancer treatments, such as fatigue, psychological distress, and adverse impact on body composition, as well as improving physical function and quality of life (QOL) [5-7]. In addition, increased physical activity is associated with improved survival and reduced disease recurrence [8]. The evidence supports the unequivocal role of physical activity in self-management [5]. Physically active cancer survivors report a sense of regaining control of their lives [9,10] and some normalcy [9-11] following a cancer diagnosis.

Engaging in physical activity is not only recommended but also safe both during and after cancer treatments [7]. The American College of Sports Medicine [7] advises that cancer survivors avoid inactivity and return to typical daily activities as soon as possible after surgery and during and after cancer treatments, working toward the standard age-appropriate physical activity guidelines [7,12]. Despite these benefits, only 23% of cancer survivors in England are active at recommended levels, and 31% are completely inactive [13].

Wang and colleagues [14] report that cancer survivors in Scotland are less likely to smoke, more likely to eat a healthy diet, and more liable to drink alcohol responsibly, although the odds ratios for these conclusions are not compelling. Wang and colleagues [14] also report that cancer survivors in Scotland are less likely to take part in at least 2 hours of physical activity than those who have not had a cancer diagnosis. A cancer diagnosis may offer a teachable moment in which people may be more receptive to changing their lifestyle behaviors [15-18]. McBride and colleagues [18] suggest that low-level interventions may facilitate such an opportunity.

### Self-Efficacy and Self-Identity

Self-efficacy is central in overcoming the barriers faced by cancer survivors in becoming physically active [19]. Self-efficacy is defined in this context as the confidence of a cancer survivor that he or she has the ability and capacity to be more physically active. Self-efficacy has been reported to be a predictor of intentions to change physical activity in cancer survivors [9,20], consistent with the extant general literature on health behavior change [21]. In addition, identifying as a physically active individual has been reported to be an indicator of physical activity engagement, with those cancer survivors who are physically activity before their diagnoses being more likely to be so afterwards [9]. However, physical activity tends to decrease following diagnosis [22] and is unlikely to reverse without intervention. These predictors of physical activity are reported to be consistent across cancer survivors regardless of age, stage, type of cancer, comorbidity, or treatment received [9].

### Remote Support to Facilitate Physical Activity Behavior Change

Cancer survivors report a high level of interest in lifestyle interventions [20,23-25]; however, access to face-to-face programs is not always possible because of transportation issues and geographic and access considerations [24]. There is a demand for written health information to support behavior change [24,26-28]. Advantages include message consistency, ease of delivery, self-paced learning, and the permanence of information with low production costs [29].

Home-based interventions using printed materials offer a cost-effective, potentially promising means of intervening regardless of location [23,24]. At a time when spending on public health and health care in the United Kingdom continues to be constrained, with demand for services increasing, the need for home-based interventions is growing. Randomized control trials (RCTs) have been, and continue to be, conducted on the efficacy of such interventions [23,30]. However, none has included a process evaluation to contextualize the use of such interventions in a real-world setting removed from the health care environment.

### The Move More Pack and its Revision

The UK charity, Macmillan Cancer Support, developed a printed resource in 2011 called the Move More Pack that aimed to effect change in physical activity in cancer survivors. The Move More Pack consisted of a physical activity and cancer booklet and a series of written assignments to support behavior change. No additional assistance or follow-up was provided. The effectiveness of the Move More Pack in effecting change in physical activity in cancer survivors has not yet been investigated.

The principal investigator led the redevelopment of the Move More Pack in 2016 to become a printed resource supported by a series of Internet-based tools. Following discussions with cancer survivors [9,31], a systematic search and critical appraisal of the literature, a review of the original Move More Pack with respect to its underlying theoretical constructs, and an inventory of the behavior change techniques (BCTs) it advocates, recommendations were made.

The theory of planned behavior (TPB) [15,32] and the social cognitive theory (SCT) [33-35] were identified as appropriate theories upon which to base the redevelopment of the Move More Pack. The original Move More Pack was assessed using the constructs of the TPB and the SCT. The BCT taxonomy version 1 (BCTTv1) [36] identified the active ingredients that aimed to effect change and those that might be missing from the original design. Following an iterative process, a group of six subject experts including the principal investigator, in partnership with Macmillan Cancer Support’s information development team, refined the structure, content, and BCTs included within the revised Move More Pack. Macmillan Cancer Support’s information development team wrote the final copy of the revised Move More Pack. [name], Macmillan Cancer Support’s chief medical editor, approved the final version. The revised Move More Pack received the National Health Service England (NHS England) Information Standard [37]. A PDF of the revised Move More Pack is included as Multimedia Appendix 1.

The revised Move More Pack retained the physical activity and cancer booklet (Multimedia Appendix 2). A pull-out wall chart is included in the revised Move More Pack for users to track their progress, record achievements, and serve as a visual prompt to be more active (Multimedia Appendix 3). Furthermore, five activity leaflets (Multimedia Appendix 4) are included on popular activities of gardening, walking, and recreational swimming; the sports of badminton, bowls, cycling, golf, and walking football; and finally, on how to be generally active in daily life [38]. A digital versatile disc that focuses on exercise specifically for cancer survivors is included and is also available to view on the Web [39].

Tailored multi-component interventions are likely to be most effective in effecting lifestyle behavior change in cancer survivors [35,40,41]. Users of the revised Move More Pack can sign up to receive e-newsletters, with messages tailored to their reported prediagnosis levels of physical activity, and influenced by the stages of physical activity behavior change advanced by Marcus and Forsyth [42]. Prediagnosis levels of physical activity are collected using the Godin Leisure Time Exercise Questionnaire (GLTEQ) [43]. Case studies included within the e-newsletters are tailored to the age and gender of the user of the revised Move More Pack. A welcome email is sent to users of the revised Move More Pack, followed by e-newsletters sent during months 1, 2, 3, 6, 9, and 12. Details are outlined in Table 1, with an example e-newsletter included as Multimedia Appendix 5.

An online social community aims to link users of the revised Move More Pack, enabling social learning and enhancing social norms [44]. An online *ask the physio* group is available and allows users of the revised Move More Pack to post questions on an open forum to a registered cancer specialist physiotherapist [45]. Details of how to find local physical activity opportunities are also included on the Web [46].

The use of a pedometer combined with a printed resource has been reported to be effective in increasing physical activity in breast cancer survivors [32]. Consequently, details are provided on how to download a straightforward and easy to use digital pedometer app, as well as an app to reduce sitting time [47]. Finally, a series of video case studies of cancer survivors who have become more active are included [48]. A Web page dedicated to users of the revised Move More Pack links to these Internet-based tools (Multimedia Appendix 6) [49].

The revised Move More Pack and Internet-based tools have been developed based on the best available evidence and following guidance on the development of complex interventions from the United Kingdom based Medical Research Council (MRC) [50]. The revised Move More Pack does not prescribe physical activity; rather, it aims to empower cancer survivors to increase control over their physical activity behavior.

### Aims

This study aims to investigate the effect of the revised Move More Pack over 24 weeks. It is hypothesized that use of the revised Move More Pack increases physical activity in cancer survivors, and the proportion of cancer survivors who are classified as active over 12 weeks increases with its use, with changes being maintained at 24 weeks. The primary aim is to test the effectiveness of the revised Move More Pack in reclassifying cancer survivors categorized as inactive or moderately active at baseline, to being more active over 12 weeks, with increases maintained at 24 weeks.

The secondary aims include:

Test the effect of the revised Move More Pack on the self-efficacy and health-related QOL (HRQOL) of cancer survivors.Analyze subgroups to elucidate for whom the revised Move More Pack has a positive effect on physical activity, self-efficacy, and HRQOL in the context of prediagnosis levels of physical activity and baseline self-efficacy.Conduct a process evaluation to contextualize the use and perceived usefulness of the revised Move More Pack.

**Table 1 table1:** The theme and behavior change techniques used in the e-newsletters sent to users of the revised Move More Pack.

Newsletter		Stage of change^a^	BCTs^b^ used^c^
**For those active before diagnosis**^d^			
	Month 1	Doing some physical activity	Information about others’ approval; Information about health consequences; Information about emotional consequences; Graded tasks; Social comparison; Goal setting (behavior)
	Month 2	Doing some physical activity	Information about others’ approval; Information about health consequences; Information about emotional consequences; Framing or reframing; Graded tasks
	Month 3	Doing enough physical activity	Information about others’ approval; Social support (unspecified); Self-reward; Action planning
	Month 6	Making physical activity a habit	Self-monitoring; Action planning; Habit reversal; Habit formation
	Month 9	Making physical activity a habit	Self-monitoring; Action planning; Habit reversal; Habit formation; Social support (unspecified)
	Month 12	Making physical activity a habit	Self-monitoring; Action planning; Habit reversal; Habit formation; Social support (unspecified); Self-reward
**For those inactive before diagnosis**^d^			
	Month 1	Inactive and thinking about becoming physically active	Information about others’ approval; Information about health consequences; Information about emotional consequences; Graded tasks; Social comparison
	Month 2	Doing some activity	Information about others’ approval; Information about health consequences; Information about emotional consequences; Framing or reframing; Graded tasks
	Month 3	Doing some activity	Information about others’ approval; Goal setting (behavior); Self-reward; Action planning; Commitment
	Month 6	Doing enough physical activity	Self-monitoring; Action planning
	Month 9	Making physical activity a habit	Self-monitoring; Action planning; Habit formation; Social support (unspecified)
	Month 12	Making physical activity a habit	Self-monitoring; Action planning; Habit reversal; Habit formation; Social support (unspecified); Self-reward

^a^On the basis of the stage of change constructs offer by Marcus and Forsyth [42].

^b^BCT: behavior change technique.

^c^BCT selected from the BCT Taxonomy version 1 [36].

^d^Prediagnosis levels of physical activity assessed using question two of the Godin Leisure Exercise Time Questionnaire.

## Methods

Identifying the underlying theoretical constructs of a health-related program is key when designing its evaluation [51]. A breakdown of the components of the revised Move More Pack based on the constructs of the SCT and the TPB, along with the BCTs used in available as Multimedia Appendix 7.

### Design

This study is a two-arm waiting list RCT (ISRCTN 66418871) with embedded process evaluation, designed following guidance from the MRC for evaluating complex interventions [52]. Figure 1 shows the progress through the phases of this study. The control arm participants receive brief physical activity information and details of the UK guidelines for physical activity. Intervention arm participants receive brief physical activity information, the revised Move More Pack, directions to the Internet-based tools, as well as the e-newsletters as outlined in Table 1, up to and including the newsletter sent in month 3.

### Sample size

NHS England [13] report that 23% of cancer survivors are active to the recommended levels for aerobic activity, 31% are inactive, and 46% are physically active but not to the recommended levels. NHS England [13] also reported that 18% of cancer survivors are interested in becoming more active. The sample size for this study has been calculated based on the assumption that the revised Move More Pack will increase the proportion of the sample achieving the aerobic physical activity guidelines by 18%. A sample of 82 participants will be required per arm for a one-tailed test, power of 80% with alpha set at 5%. A total of 99 participants will be recruited per arm to allow for a 20% dropout.

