### Recruitment

Participants will be recruited by email invitation through the Macmillan Cancer Support database of cancer survivors. An advert will also be placed on the Macmillan Cancer Support Facebook page [53]. Those that express an interest will be sent further participant information by email, with consent provided digitally by check box, following the British Psychological Society ethics guidance for Internet-mediated research [54]. Participants will be informed that the study aims to investigate the impact of health promotion information on lifestyle behaviors, with no specific reference made to physical activity. Participants will be notified that they will be randomized to receive guidelines for a lifestyle behavior or a health promotion pack with Internet-based tools relating to a lifestyle behavior. Recruited participants will be randomized based on simple randomization. Recruitment will continue until 99 participants are randomized to either the control or intervention arm.

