### Data Analysis

The quantitative data will be analyzed using intention-to-treat analysis. The GLTEQ provides a physical activity score, and these scores can be used to categorize participants into inactive, moderately active, and active groups. The two-proportion *z* test is used to investigate differences between the proportions of participants in the control arm and the intervention arm classified as active.

Secondary analysis of the paired before and after ordinal data within each intervention arm will be analyzed with the Wilcoxon’s signed-rank test; across arms, comparisons will be analyzed with the Mann-Whitney *U* test. The mean GLTEQ scores will be analyzed with the independent *t* test and the paired *t* test. The predictors of self-efficacy and prediagnosis physical activity on post-intervention physical activity levels will be assessed by multiple regression analysis. Additional quantitative data will include descriptive statistics such as means, standard deviations, medians, and percentages.

The interviews will be recorded and transcribed verbatim. The interview transcripts and the qualitative comments made by the participants as part of the questionnaires administered at the 12-week and 24-week time points will be thematically analyzed [61] by two of the study investigators, ensuring that identified themes are grounded in the original data. A third investigator will be used where there are differences in opinion. The process of analysis will follow five stages:

Familiarization with the data involving reading and rereading the interview transcripts and qualitative comments.Initial coding.Theme identification.Theme review and development of higher level categories.Identification of relationships and patterns.

The investigators will move back and forth through these steps until they concur and are satisfied with the themes, categories, relationships, and patterns identified.

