The major limitation of this study is the use of self-reported measures to assess and evaluate participants’ physical activity, self-efficacy, and HRQOL. The measures selected are validated and reliable. The GLTEQ has been used in previous research with cancer survivors [57], and the FACT-G7 is specifically designed for cancer survivors [58]. The self-reported measures have been selected for their ease of implementation in a real-world setting. Whereas the use of an objective measure of physical activity may be preferable, this would introduce an additional behavior change technique. Furthermore, as the revised Move More Pack aims to enable cancer survivors to monitor their physical activity by directing them to use a pedometer, introduction of an objective measure may influence the effectiveness of this component of the revised Move More Pack.

Some studies of cancer survivors have reported high levels of dropout [69]. Therefore, an additional 20% will be recruited to this study. Furthermore, a combination of strategies will be employed to encourage participants to complete the relevant questionnaires at the data collection points, including email and text reminders.

It is possible that the exclusion criteria for this study may result in a selection bias; however, the safety of the participants will not be compromised. In addition, as participants are recruited through the channels of Macmillan Cancer Support, they may not be representative of the population of cancer survivors in the United Kingdom. The profile of the included participants will be reported and any selection bias identified.

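### The 20% dropout allowance is computed as 82 × 1.2 instead of 82 / 0.8, so 99 per arm falls about 3 completers short of the required 82 (minor)

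*Protocol article*

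**What the plan says.** The Sample size section takes from a national survey that "23% of cancer survivors are active to the recommended levels for aerobic activity" and assumes that the revised pack "will increase the proportion of the sample achieving the aerobic physical activity guidelines by 18" percent. The requirement follows: "A sample of 82 participants will be required per arm", "for a one-tailed test, power of 80% with alpha set at 5" percent. The dropout step comes next: "A total of 99 participants will be recruited per arm to allow for a 20% dropout".

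The limitations part of the Discussion describes the same allowance differently. After noting that some studies in cancer survivors had high dropout, it says: "Therefore, an additional 20% will be recruited to this study".

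The Abstract repeats 99 per arm, and so does the Recruitment section: "Recruitment will continue until 99 participants are randomized to either the control or intervention arm". No section gives another dropout rate or another basis for 99.

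**The concern.** Allowing for a 20% dropout is not the same as recruiting 20% extra. The first asks how many must be randomized so that 82 remain after one in five is lost. The second adds a fifth of 82, and that is too few, because the loss then applies to the enlarged number.

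The Sample size section claims the first, but its figure comes from the second, and the Discussion sentence confirms this. Because 82 gives 80.0% power with no slack, any shortfall in completers takes the power below the stated value. What is at stake is whether the quoted pair, 20% dropout and 80% power, is true of the design.

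**Working it through.** **Inputs (Sample size section).** Control proportion p1 = 0.23. The article does not label it as the control rate, but it reproduces the stated size. Intervention proportion p2 = 0.23 + 0.18 = 0.41. One-tailed alpha 0.05 (z = 1.645), power 0.80 (z = 0.842), required n = 82 per arm, recruited n = 99 per arm, dropout 20%. The Data Analysis section names the two-proportion z test.

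**Step 1: reproduce 82.** Pooled-variance formula without continuity correction, with mean proportion (0.23 + 0.41)/2 = 0.32:

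n = [1.645 × √(2 × 0.32 × 0.68) + 0.842 × √(0.23 × 0.77 + 0.41 × 0.59)]² / 0.18²

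= [1.645 × 0.6597 + 0.842 × 0.6473]² / 0.0324 ≈ 82.0

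The stated 82 is correct on the plan's own inputs, so the error lies only in the dropout step.

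**Step 2: reproduce 99.**
- Multiplying: 82 × 1.2 = 98.4, rounded up to 99. This matches the article.
- Dividing: 82 / (1 − 0.20) = 102.5, rounded up to 103. This does not match.

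**Step 3: what 99 delivers.**
- Completers after 20% dropout: 99 × 0.8 = 79.2, about 79 per arm, or 82 − 79 = 3 short.
- Largest dropout that still leaves 82: 1 − 82/99 = 17.2%.
- Check on 103: 103 × 0.8 = 82.4, which meets the requirement.

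**Step 4: power at 79.** Power = Φ{[0.18 × √n − 1.645 × 0.6597] / 0.6473}, one-tailed 5%, 23% versus 41%.

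| Method | n = 82 | n = 79 |
|---|---|---|
| Pooled z formula (reproduces the plan) | 80.0% | 78.7% |
| Arcsine | 80.2% | 78.9% |
| Unpooled z formula | 80.9% | 79.6% |
| Exact enumeration of the z test | 80.8% | 79.3% |

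On every method power at 79 is below 80%. On the plan's own formula the loss is 80.0 − 78.7 = 1.3 percentage points.

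**The case against.** **The shortfall is trivial.** Three completers per arm and about 1.3 points of power are well within the uncertainty of the 23% and 18% assumptions. That stands, and it sets the weight of the point. It does not make the sentence correct.

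**Adding 20% is a recruitment convention.** The Discussion sentence alone could be read that way. The Sample size section cannot: it says that 99 absorbs a 20% dropout.

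**Intention-to-treat keeps everyone in the analysis.** The Data Analysis section does specify intention-to-treat, and the article does not say how missing outcomes enter the comparison; a separate analysis plan may. So 79 with outcome data is an assumption, though it is the one implied by inflating for dropout at all. The outcomes come from web questionnaires, so a non-responder has no observed value. Keeping such participants by imputation would not automatically restore power.

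**Arms of exactly 99 are not guaranteed.** Simple randomization can leave the arms unequal, so 78.7% applies to equal arms of 99 and is not a fixed property of the trial. The inflation step is wrong either way.

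**A stronger reading that the article does not support.** The Data Analysis section says that the z "test is used to investigate differences between the proportions of participants in the control arm and the intervention arm classified as active", without repeating the direction. A reader might infer a two-sided primary test and therefore a much larger loss of power. But the Sample size section fixes a one-tailed test, the Aims state a directional hypothesis, and a z test of a difference can be run one-tailed. Nothing contradicts the sizing, so there is no large power gap to report.

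Nor does the wording of the 18% increase need a finding: only the absolute reading, 23% to 41%, reproduces 82.

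**Conclusion.** The point holds as a minor arithmetic error. The article's 99 per arm does not allow for the 20% dropout it names; it allows for 17.2%. At 20% dropout about 79 per arm remain, and power for the planned one-tailed 5% test of 23% versus 41% is about 78.7%, or up to 79.6% by the other methods shown, rather than the stated 80%.

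This rests on three assumptions: dropouts contribute no outcome, the arms are equal at 99, and there is no further loss. On the last, the Ethical Considerations section omits control participants who used the pack before 12 weeks, and the allowance does not mention this.

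The base requirement of 82 is sound. The error does not support calling the trial seriously underpowered.

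**What to change.** Restate the figure in the Sample size section in one of two ways:

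- 99 participants per arm allows for a 17% dropout; or
- 99 participants per arm leaves about 79 with outcome data after a 20% dropout, giving about 79% power (one-tailed 5%, 23% versus 41%).

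Align the limitations sentence in the Discussion, so that it no longer equates recruiting an extra fifth with covering a 20% dropout. State that the calculation assumes dropouts contribute no outcome.

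If the sponsor wants both 20% dropout and 80% power to hold, the matching size is 103 per arm: 206 in total instead of 198, or 8 more participants. The Abstract and Recruitment figures would then change too.

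Restating costs wording only, with a slightly less favourable stated figure. The design and the primary test are unchanged.
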